## 4.4 Sample size calculation

We will perform linear regression analysis for our primary outcome measure. Including our potentially confounding covariates, a total of 12 variables will be included in the model. The variables will be injury of the chorda tympani nerve, age, gender, smoking, weight, gastroesophageal reflux, olfactory dysfunction, salivary hypofunction, medication, rhinosinusitis/allergic rhinitis, previous COVID-19 and diabetes mellitus (12–22). We have calculated that these variables are 14 degrees of freedom in total. We will include 10 patients per degree of freedom in our linear regression model. To anticipate withdrawal of 10% of participants, we will include an extra 14 patients which means we will need a sample size of 154 patients.

At the ENT department at the UMCU, 80 otosclerosis patients undergo primary stapes surgery per year and 100 patients undergo cochlear implantation per year. Assuming a participation rate of 70%, we expect to able to include 154 patients in 15 months’ time.

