# 5. NON-INVESTIGATIONAL PRODUCT 5.1 Taste Strip Test

We will also use the TST to investigate the taste ability. This objective taste test is validated in a population of healthy individuals by Mueller et al. The test will be performed according to their technique (30). The researcher will use filter paper strips, which are impregnated with four concentrations of sweet (0.4, 0.2, 0.1, and 0.05 g/mL sucrose), sour (0.3, 0.165, 0.09, and 0.05 g/mL citric acid), salty (0.25, 0.1, 0.04, and 0.016 g/mL sodium chloride), bitter (0,006, 0.0024, 0.0009, and 0.0004 g/mL quinine hydrochloride) and umami (0.03, 0.06, 0.12 and 0.25 g/mL sodium L glutamate monohydrate) tastes. Two blanked taste strips will also be used. We will present the strips in increasing concentrations in a randomized order to each side of the anterior tongue. The patient has to identify which one of the five flavours the strip is. The patient has to keep the tongue out of the mouth with the taste strip on the tongue, until he/she has made his decision by pointing to one of the five descriptors (sweet, sour, salty, bitter or umami) of the list. We will use 42 taste strips, because we want to test the taste ability of both sides of the tongue (30). Between the assessments of the taste strip the mouth will be rinsed with water. With this information we can compare the gustatory function of the area of the tongue that is innervated by the potentially injured CTN with the gustatory function of the contralateral area of the tongue. The patient will undergo this test preoperatively, 1 week, 6 weeks and 6 months postoperatively. Patients will be asked not to eat, drink (except for water), smoke or brush their teeth one hour before beginning the taste test (30). The taste strips will be ordered from Burghart Messtechnik (Germany).

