## 8.1 Primary study parameter

The primary study parameter is the change in the amount of identified taste strips by patient, preoperatively and 6-8 weeks postoperatively. This outcome will be presented continuous with a range from 1 to 20 identified taste strips. Mean (or the median) and standard deviation (or the range) will be reported. The effect of CTN injury on the amount of identified taste strips will be evaluated using linear regression analysis. The following confounding variables will be included in the analysis: age, gender, smoking, weight, gastroesophageal reflux, olfactory dysfunction, salivary hypofunction, medication, rhinosinusitis/allergic rhinitis, previous COVID-19 and diabetes mellitus (12–22).

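### The primary regression omits the preoperative ipsilateral taste-strip score: precision is lost under either outcome definition, and baseline differences stay in the injury effect if the outcome is the 6-week score

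*Protocol*

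**What the plan says.** Protocol section 4.4 closes the list of model terms: "Including our potentially confounding covariates, a total of 12 variables will be included in the model". It names them ("The variables will be injury of the chorda tympani nerve, age, gender, smoking, weight, gastroesophageal reflux, olfactory dysfunction, salivary hypofunction", then medication, rhinosinusitis or allergic rhinitis, previous COVID-19 and diabetes) and counts them: "We have calculated that these variables are 14 degrees of freedom in total". The sample size rests on that count: "We will include 10 patients per degree of freedom in our linear regression model". Section 8.1 repeats the same eleven covariates: "The following confounding variables will be included in the analysis: age, gender, smoking, weight, gastroesophageal reflux, olfactory dysfunction, salivary hypofunction, medication", and so on. No section adds the preoperative taste-strip score.

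The score is available. Of the taste-strip test, section 5.1 says "The patient will undergo this test preoperatively, 1 week, 6 weeks and 6 months postoperatively", and section 6.3 schedules the preoperative session for all participants.

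The outcome is described in two ways. Section 6.1.1 makes it the ipsilateral score at 6 weeks, from 0 to 20. Section 8.1 opens by calling it the change from before surgery to 6-8 weeks. It then gives a range of 1 to 20 and regresses the number of strips identified, which fits a score; a change would run from -20 to 20.

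Section 6.2 states that there is no randomisation. Section 3 gives three injury categories: untouched, mobilised and sectioned.

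**The concern.** A patient's own score on the same test and the same side of the tongue before surgery is the obvious candidate predictor of the score afterwards. The plan spends degrees of freedom on reflux, weight and allergic rhinitis but not on this score. The injury category arises at operation, and two surgical populations are pooled without type of surgery among the covariates, so the groups may differ in taste before surgery.

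The stake is the primary estimate. On the post-score reading, a baseline difference passes into the injury effect. On the change reading, baseline is subtracted in full whether or not the data support a slope of 1. Section 1 reports that earlier studies disagree on whether sectioning or stretching is worse, so an error of half a strip, or a needlessly wide interval, could matter to the conclusion.

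**Working it through.** **The plan's own figure.** 14 df x 10 = 140; 140 + 14 = 154. This reproduces the stated sample size. It comes from a patients-per-df rule, so no SD, effect size or pre-post correlation is available.

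**Precision.** Let r be the pre-post correlation given the other covariates, assume equal pre and post SDs, and set the variance of the post-score to 1. The baseline slope is then r. Subtracting k times baseline leaves residual variance (1 - r²) + (k - r)²:

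- post-score alone (k = 0): 1
- change (k = 1): 2(1 - r)
- baseline as covariate (k = r): 1 - r²

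The last is the smallest for every r strictly between 0 and 1. Its ratio to the change analysis is (1 - r²) / [2(1 - r)] = (1 + r)/2.

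| assumed partial r | post-score | change | adjusted | adjusted / post | adjusted / change |
|---|---|---|---|---|---|
| 0.3 | 1.00 | 1.40 | 0.91 | 0.91 | 0.65 |
| 0.5 | 1.00 | 1.00 | 0.75 | 0.75 | 0.75 |
| 0.7 | 1.00 | 0.60 | 0.51 | 0.51 | 0.85 |

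**Baseline differences.** Let d be the baseline difference between two injury groups, e the true injury effect and b the within-group baseline slope. Two assumptions about what would happen without injury give different answers:

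| expected estimate | post-score | change | adjusted |
|---|---|---|---|
| A: baseline difference carries forward with slope b | e + bd | e - (1 - b)d | e |
| B: baseline difference is stable over time | e + d | e | e + (1 - b)d |

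With assumed e = -2, d = -1 and b = 0.5:

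- A gives -2.5, -1.5 and -2.0. A simulation built on A (140 patients, three groups, assumed SD 3.5, 4000 runs) gave -2.52, -1.51 and -2.02.
- B gives -3.0, -2.0 and -2.5.

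The unadjusted post-score is off under both. Change and baseline adjustment are each right under one.

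**Score or change.** If Y = a + g x injury + b x baseline + other terms, then Y - baseline = a + g x injury + (b - 1) x baseline + other terms. The injury coefficient g is the same, so with baseline in the model it no longer matters which outcome is written down.

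**Cost in df.** The preoperative score adds one term: 15 df, and 140/15 = 9.3 evaluable patients per df. Keeping ten per df would need 150 evaluable patients: 165 with the protocol's way of adding 10%, or 150/0.9 = 167.

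**The case against.** The strongest reply is that section 8.1 does use baseline, because its first sentence defines the outcome as a change. In a non-randomised study a change score can be the unbiased analysis: under B above it is right and the adjusted model is off by half a strip. The simulation was generated under A, so it cannot decide between the two. This stands. A reader might infer that baseline imbalance biases the planned estimate on either reading, or that change always over-corrects. The documents support neither inference. They also do not show that the groups do differ at baseline or that baseline taste influences how the nerve is handled.

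A reader might also take from the table that a third more patients are needed (1/0.75 = 1.33). That holds only at a partial correlation of 0.5 with equal SDs. The eleven covariates were chosen as influences on taste and may absorb part of the correlation. For example, if the marginal correlation is 0.5 and one covariate predictor explains 30% of each score, the partial value is (0.5 - 0.3)/0.7 = 0.29. The variance is then 0.92 of the post-score analysis, a gain of about 8%, although it is (1 + 0.29)/2 = 0.64 of the change analysis. Nerve injury may also alter the postoperative SD.

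Nor is the change free, since one more df takes the plan below its own ten per df.

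Finally, section 5.1 says of testing both sides "With this information we can compare the gustatory function of the area of the tongue that is innervated by the potentially injured CTN" with the other side. That states what the data allow and promises no model, so its absence from section 8 is not an error.

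What does not stand is that the matter is left to a statistical analysis plan. The protocol lists the model twice and sizes the study on its df, so a later plan that added baseline would depart from both sections.

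**Conclusion.** The point holds in a limited form. The closed model omits a baseline value that is already being collected.

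- Under 6.1.1 and the regression sentence of 8.1, any baseline difference between injury groups stays in the injury effect, and precision is lost.
- Under the first sentence of 8.1, precision is still lost whenever the baseline slope is below 1. Regression-to-the-mean bias is possible but conditional on group differences not being stable.

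The gain from adjustment is a residual variance of 0.51 to 0.91 of the post-score analysis, or 0.65 to 0.85 of the change analysis, for partial r of 0.3 to 0.7. These figures are illustrative: they assume equal SDs and a correlation that the documents do not give. The direction of the precision result does not depend on the value of r between 0 and 1. The stated sample size of 154 reproduces and is not itself in error.

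**What to change.** In section 8.1, regress the 6-week ipsilateral score on CTN injury (three categories), the preoperative ipsilateral score and the listed confounders. Report the unadjusted change score as a sensitivity analysis, and say that the two rest on different assumptions about group differences over time.

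The score-versus-change conflict between 6.1.1 and 8.1 then no longer affects the injury estimate. The assessment window (6 weeks in 6.1.1, 6-8 weeks in 8.1) must still be reconciled.

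In section 4.4, add the score to the variable list and restate the count as 15 df. Then either state about 9.3 evaluable patients per df at 154, or drop one weaker covariate and stay at 14 df. Holding to ten per df would instead mean 165 to 167 patients.

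No new measurement or visit is needed. A model that also uses the contralateral side is optional and not part of this change.

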# 3. STUDY DESIGN

This study concerns a prospective study including patients who will undergo primary stapes surgery or primary cochlear implantation. The study will be performed at the department of Otorhinolaryngology in the UMCU.

The objective of this study is to evaluate the effect of CTN injury on postoperative taste function. CTN injury is a categorical variable with three categories: no touch, mobilisation and completely sectioned.

The study design is illustrated in Figure 1. Patients participate after Informed Consent (IC) is obtained. It will run for approximately two years in the UMCU. Evaluation will take place preoperatively and at 1 week, 6 weeks and 6 months postoperatively by means of taste strip test (TST), electrogustometer (EGM), Macronutrient and Taste Preference Ranking Task (MTPRT) and questionnaires (AHSP questionnaire, Health related quality of life questionnaire and a supplementary questionnaire on taste perception). Preoperatively and 1 week postoperatively the patient’s olfactory function will be evaluated using the Sniffin’ Sticks test. Three months after surgery the taste sensation is evaluated at home using questionnaires. The questionnaires will be sent by Castor or on paper. The contents of these evaluations will be explained in detail in the ‘Investigational products’ and ‘Methods’ section of this protocol.

[figure not shown]

**Figure 1.** Flowchart study procedures. TST: taste strip test, EGM: electrogustometer, AHSP: appetite, hunger and sensory perception, MTPRT: macronutrient and taste preference ranking task The symbol
[figure not shown]
 means that three months after surgery the taste sensation will be evaluated at home using three questionnaires.

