### 6.1.3 Other study parameters

Baseline characteristics (age, gender), medical history and details concerning the surgical procedure that was performed.

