## 6.2 Randomisation, blinding and treatment allocation

There will be no randomization. The patient and outcome assessor are blinded to the predictor variables, including the presence or absence of CTN injury. The surgeon will complete an electronic Case Report Form (eCRF) in Castor, including the predictor variable CTNinjury. Both patients and researchers will not be informed about the CTN injury until the patient has finished all evaluations. The eCRF will be locked to read for the researchers and the surgeon will not report the CTN injury in the surgery report. After a patient has completed all evaluations, the investigator will read the eCRF and report the CTN injury in the electronic patient record. We do not expect that there are circumstances that require us to unblind the patient or the outcome assessor during the study.

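### The primary regression pools stapes surgery and cochlear implantation without a term for type of operation, so the estimated effect of nerve injury can be confounded by procedure

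*Protocol*

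**What the plan says.** Section 3 describes the cohort: "This study concerns a prospective study including patients who will undergo primary stapes surgery or primary cochlear implantation". Exposure is observed, not assigned. Section 6.2 says "There will be no randomization", and section 3 says "CTN injury is a categorical variable with three categories: no touch, mobilisation and completely sectioned".

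Section 8.1 sets the primary analysis: "The effect of CTN injury on the amount of identified taste strips will be evaluated using linear regression analysis". The confounders it names are "age, gender, smoking, weight, gastroesophageal reflux, olfactory dysfunction, salivary hypofunction, medication, rhinosinusitis/allergic rhinitis, previous COVID-19 and diabetes mellitus". Section 4.4 gives the same 11 covariates, counts them with CTN injury as 12 variables and 14 degrees of freedom, and derives the total of 154 from that count. The list is therefore closed, and type of operation is not on it.

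Section 4.4 shows that both operations contribute substantially: "80 otosclerosis patients undergo primary stapes surgery per year and 100 patients undergo cochlear implantation per year". The operation is recorded. Section 2 lists surgical details among the other parameters, and section 6.1.3 lists "details concerning the surgical procedure that was performed". Neither place assigns them to a model, and section 8.3 plans only descriptive summaries. The protocol states no stratification by operation, no analysis by operation and no injury-by-operation term.

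**The concern.** Without randomisation, covariate adjustment is the main protection the protocol offers against confounding of the injury effect. Injury arises during the operation, and there are two different operations done in patients with different indications. Two conditions would together bias the injury coefficient:

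- the mix of untouched, mobilised and sectioned nerves differs between stapes surgery and cochlear implantation;
- the operation, or the kind of patient who has it, affects the taste-strip score by a route other than the nerve and other than the listed covariates.

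If both hold, part of a difference between procedures would be reported as an effect of nerve injury. That coefficient answers the primary objective. An analysis plan that followed the protocol's list would carry the omission forward, because the list is fixed here and the sample size is built on it.

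**Working it through.** **1. The protocol's own figure.** Inputs from section 4.4: 14 degrees of freedom (df), 10 patients for each, 10% withdrawal added as 14 patients. 14 × 10 = 140, and 140 + 14 = 154. This is reproduced, and the count leaves no df for operation.

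**2. Mix of operations.** From section 4.4, with equal participation assumed: 154 × 80/180 = 68.4 stapes and 154 × 100/180 = 85.6 implant patients. Neither group is small enough to ignore.

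**3. Form of the bias.** With operation left out, approximately:

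bias = (difference in implant share between injury groups) × (effect of operation on the score not due to the nerve)

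The documents give neither factor. If either is 0, the bias is 0. With an assumed share difference of 0 to 0.6 and an assumed operation effect of 0 to 2 strips, the bias runs from 0 to 0.6 × 2 = 1.2 strips.

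**4. Check by simulation.** Assumptions: true injury effect zero, 140 completers, implant share 100/180, residual SD 4, two injury groups (sectioned or not), no other covariates, implant patients scoring lower by the stated number of strips, 3,000 runs per scenario. The sectioning rates, operation effects, SD and sign are all assumed.

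Implant shares follow from the sectioning rates. For 20% (stapes) and 40% (implant):
- among sectioned: 0.4 × 0.556 / (0.4 × 0.556 + 0.2 × 0.444) = 0.714
- among not sectioned: 0.6 × 0.556 / (0.6 × 0.556 + 0.8 × 0.444) = 0.484
- difference: 0.230

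For 10% and 50% the shares are 0.862 and 0.410, a difference of 0.452.

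| Sectioned, stapes / implant | Operation effect (strips) | Bias by formula | Bias simulated | False positives, operation omitted | False positives, operation included |
|---|---|---|---|---|---|
| 30% / 30% | 1 to 3 | 0 | about 0 | about 5% | about 5% |
| 20% / 40% | 1 | -0.23 | -0.23 | 6.0% | 5.1% |
| 20% / 40% | 2 | -0.46 | -0.47 | 10.7% | 5.5% |
| 20% / 40% | 3 | -0.69 | -0.65 | 13.1% | 5.9% |
| 10% / 50% | 1 | -0.45 | -0.44 | 9.8% | 5.2% |
| 10% / 50% | 2 | -0.90 | -0.89 | 21.9% | 4.9% |
| 10% / 50% | 3 | -1.36 | -1.38 | 43.0% | 4.4% |

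The last row exceeds 1.2 strips only because it assumes an operation effect of 3. With operation in the model, the simulated bias was within 0.04 strips of zero in every scenario.

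**5. Cost of the extra term.** 14 + 1 = 15 df. At 140 completers, 140/15 = 9.3 patients per df. Under the protocol's own rule, 15 × 10 = 150 and 150 + 15 = 165. Recruitment at section 4.4's rates is 180 × 0.7 / 12 = 10.5 per month, so 154 patients take 14.7 months and 165 take 15.7, against the 15 months stated.

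**6. Cost in precision.** For two equal injury groups with implant shares of 80% and 20%, the squared correlation between injury and operation is 0.6² = 0.36. The variance inflation is 1/(1 − 0.36) = 1.56, and the standard error rises by a factor of √1.56 = 1.25. The exposure has three categories, so this is a guide only.

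**The case against.** The case for leaving the model alone has real content.

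- **Neither condition for bias is documented.** The protocol reports no injury rates and no taste scores by operation. Its only remark on why a nerve might be sacrificed, in section 1, concerns the surgeon's view of the middle ear and is not tied to either operation. This stands: confounding is a possibility, not a finding.
- **Much of what an operation does to taste on that side of the tongue may run through the nerve.** Section 1 says the nerve supplies the anterior two-thirds of the same side. An effect by that route is the exposure itself and not confounding. This stands as a reason to think the remaining operation effect could be small. It does not show that it is zero.
- **Parts of the plan already help.** Section 8.1 defines the outcome as change from the preoperative score, so stable differences in baseline taste between the two patient groups largely cancel. Age, gender, medication, salivary function and comorbidities are adjusted for. Section 5.1 tests both sides of the tongue. The help is partial. Section 6.1.1 defines the outcome as the 6-week score and not the change, the opposite side is not in the primary model, and none of the listed covariates captures differences due to the operation itself.
- **The operation is recorded and could still be added at analysis.** True, but the protocol states the model twice and counts its terms, so the place to add it is the protocol.

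**Conclusion.** The primary model omits type of operation, and the CTN injury effect can therefore be confounded by procedure. The omission is certain from sections 4.4 and 8.1. The bias is not: its size and direction cannot be obtained from the documents, and zero is among the possible values. The range of 0 to about 1.2 strips, and the false-positive rates above, illustrate assumed inputs and do not estimate this study.

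A reader might infer more: that the injury effect is confounded, that the operation is what mainly decides how the nerve is handled, or that a bias of some minimum size must exist. The documents support none of these, because they give no injury distribution by operation and no operation effect apart from the nerve. Nor do they support calling the listed covariates useless. A covariate that predicts taste can improve precision and correct chance imbalance even if it has no bearing on nerve handling.

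Severity: should fix. The change is cheap, uses a variable already collected, and protects the primary estimate.

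**What to change.** - Add type of operation (stapes surgery or cochlear implantation) as a covariate in the primary model, in both section 4.4 and section 8.1. Make this decision before injury data are read alongside outcomes, and do not make it depend on the results.
- Restate the count as 13 variables and 15 df. Either keep 154 patients and state that this gives about 9.3 per df at 140 completers, or apply the protocol's own rule and recruit 165, about one month longer at the stated rates.
- Tabulate injury category by operation, so that readers can see how far the two overlap.
- Optionally, report the injury contrast within each operation as a sensitivity analysis. A full injury-by-operation term would use two more df (17 in total, 140/17 = 8.2 patients per df), so it should not be the primary model.

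No listed covariate needs to be dropped. Section 8.2 names no covariates for the secondary models, so there is no list there to correct.

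The cost is one df, plus a larger standard error if injury and operation are strongly associated: about 25% for two equal groups at an 80%/20% split. That loss would reflect how little the data can separate injury from procedure, which the present model would not show.
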